**Figure 2 figure2:**
[figure not shown]
iTAB interface with SMS text message selection options. iTAB: individualized Texting for Adherence Building.

**Figure 3 figure3:**
[figure not shown]
iTAB SMS text message decision system. iTAB: individualized Texting for Adherence Building.

#### Participant Monitoring

Within 2 weeks of the baseline visit, participants are contacted by an FHCSD care coordinator over the phone to discuss any issues related to receiving and responding to SMS text messages. Participants are also contacted by an FHCSD care coordinator 4 weeks prior to their in-person study visits to schedule their upcoming appointment. At interim study visits (Week 12, 24, and 36, depending on the duration of the intervention), participants are asked to complete a set of psychosocial questionnaires and discuss concerns regarding the iTAB system. Additionally, participants and care coordinators reassess SMS text message customizations at each interim clinic visit to ensure participant satisfaction with the system and to optimize ART adherence.

All SMS text messages sent (eg, reminders, reinforcement SMS text messages) and received (eg, participant responses) by the iTAB system are recorded. After 3 consecutive days of nonresponse to SMS text messages or “N” responses to prompts about medication adherence, an automated SMS text message regarding participant noncompliance to the study and to their medications is triggered. An FHCSD care coordinator attempts to contact the participant to discuss barriers to medication adherence (eg, forgetting dose time) and potential solutions (eg, pairing medication taking with another daily behavior, such as brushing one’s teeth).

The care coordinator is also able to monitor and track participants’ daily SMS text message responses to medication adherence reminders using the iTAB clinical dashboard. For ease of interpretation, the dashboard utilizes a “Stop-Light” system as a simple summary of the self-reported adherence rate (Figure 4). Adherence rates greater than 90% are displayed with a green circle, those between 70% and 90% with a yellow circle, and those less than or equal to 70% with a red circle. Furthermore, a monthly calendar summarizes past daily adherence and is color coded according to participants’ daily self-reported adherence (Figure 4). The iTAB clinical dashboard is used to facilitate conversations between the participant and care coordinators during interim clinic visits about ART adherence and to problem solve instances of nonadherence or nonresponse to SMS text messages. Information from the clinical dashboard is not shared with health care providers.

**Figure 4 figure4:**
[figure not shown]
Example of the iTAB dashboard and summary of medication adherence with the Stop-Light System. Example of iTAB Calendar Report for ART adherence and SMS text message responses. These examples are of an individual on 2 doses of medication a day, receiving 2 iTAB SMS text messages per day. ART: antiretroviral therapy; iTAB: individualized Texting for Adherence Building.

#### Outcomes

Undetectable plasma viral load and ART adherence (as measured by participants’ responses to daily SMS text messages) are the primary outcomes for this single-arm trial. In addition, participants complete an in-person comprehensive battery of psychosocial assessments at the baseline, interim, and end-of-study visits (at either Week 24 or Week 48). Specific assessments administered at each study visit are listed in Table 3. Assessments with strong reliability and validity among HIV populations were chosen, where possible. Measures collected at the baseline study visit include plasma viral load (abstracted from FHCSD electronic medical records), medication adherence behaviors (eg, percentage of adherence in the past 30 days), psychosocial risk factors associated with poor HIV-related outcomes among PWH (eg, sociodemographic characteristics, substance use, and social support), and culturally specific risks for nonadherence among African Americans (eg, subjective experiences of discrimination, HIV-related stigma, and medical mistrust). Measures collected at interim study visits (ie, every 12 weeks) are a subset of the baseline measures (eg, perceived stress, alcohol use, substance use, and depressive symptoms). Upon completion of the intervention (at either week 24 or 48), participants complete a subset of psychosocial assessments, as well as a feedback questionnaire assessing their experience, satisfaction with, and perceived usefulness of the intervention. Laboratory data on HIV-disease characteristics (eg, plasma viral load and CD4 count) and utilization of FHCSD services are collected from electronic medical records by care coordinators at each in-person study visit.

**Table 3 table3:** Assessments administered^a^

Domain		Assessments	Baseline	Week 12, 36	Week 24, 48
**HIV disease variables and antiretroviral therapy adherence**					
	Primary outcome: Viral load^b^	Data acquired from FHCSD^c^ blood draw at clinical visit	X		X
	CD4 count^b^	Data acquired from FHCSD blood draw at clinical visit	X		X
	Self-report of ART^d^ adherence	Ira Wilson Adherence Questionnaire (IWQU) [27]	X	X	X
**Factors that may impact antiretroviral therapy adherence**					
	Sociodemographic characteristics	Self-reported sex, gender, age, race, ethnicity, birth location, relationship status, HIV status disclosure, employment, income, housing stability, education	X		
	Depression symptoms	Beck Depression Inventory-II (BDI)	X	X	X
	Alcohol and illicit substance use	Alcohol Use Disorders Identification Test (AUDIT) and Drug Abuse Screening Test (DAST-10 Modified)	X	X	X
	Subjective social status	MacArthur Scale of Social Status Scale	X		
	Beliefs related to HIV medications	Beliefs Related to Medications Questionnaire	X		
	Supports and barriers to adherence	Supports and barriers to adherence	X		
	Self-efficacy for medications	Self-efficacy for managing medications and treatments	X	X	X
	Illicit substance use and sexual behaviors	Risk Questionnaire	X		X
	Collective self-esteem	Collective Self Esteem Scale	X		X
	Medical mistrust	Trust in the medical system; attitudes toward the health care	X		X
	Instrumental and social support	NIH Toolbox Emotional Support, Instrumental Support, and Loneliness scales	X		X
	Beliefs about HIV	Beliefs about HIV	X		X
	Subjective experiences of discrimination	Everyday Discrimination Scale; Multiple Discrimination Scale	X		X
	Quality of life	Medical Outcomes Study: 36-item Short Form Survey (MOS: SF-36)	X	X	X
	Personality	Ten-Item Personality Inventory	X		
	Perceptions of stress	Perceived Stress Scale	X	X	X
	Lifetime exposure to stress/adversity	Negative life events	X		
	Health care utilization	Utilization of care	X		X
	Health literacy	Short Assessment of Health Literacy-English (SAHL-E)	X		
	Stigma and psychosocial aspects of living with HIV	HIV Stigma Scale	X		
	Religiousness/Spirituality	Brief Multidimensional Measure of Religiousness and Spirituality	X		
	Cellphone Usage	Cellphone Usage Questionnaire	X		
	Medication-taking behavior^e^	Medication-Taking and Text-Responding Behavior Questionnaire			X
	Intervention feedback^e^	iC-CHANGE Feedback Questionnaire (Likert scales of feasibility, acceptability, and satisfaction)			X

^a^The X denotes those visits where the assessment will be administered.

^b^Data collected from electronic medical records from FHCSD clinical visit during the study period or provided by the participant.

^c^FHCSD: Family Health Centers of San Diego.

^d^ART: antiretroviral therapy.

^e^Administered only at the final visit.

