#### Participant Timeline

Participants receive the culturally tailored iTAB intervention, consisting of personalized SMS text messages sent daily to promote ART adherence. Participants have the option to enroll in a 24-week study with 3 visits (baseline, Week 12, and Week 24) or a 48-week study with 5 visits (baseline, Week 12, Week 24, Week 36, and Week 48). The initial visit lasts up to 3 hours and consists of completing a comprehensive battery of psychosocial assessments and setting up the iTAB intervention (eg, customizing SMS text message content and delivery time). Participants return every 12 weeks for interim visits, where they complete psychosocial assessments and discuss any concerns regarding the iTAB system with the FHCSD staff. The final study visit, at either week 24 or 48, lasts approximately 1 hour and includes completing psychosocial assessments and completing an exit interview during which participants are asked to provide feedback on the intervention (see Figure 1 for a schematic depicting the participant timeline).

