### Data Collection, Management, and Analysis

#### Data Collection Methods

The iTAB system records all SMS text messages that are sent (eg, reminders, reinforcement SMS text messages) and received (eg, participant responses). Indicators of medication adherence as well as adherence to the intervention are collected via the iTAB system.

Measures (data derived from the electronic medical record and psychosocial assessments) are collected at baseline, interim, and the final study visits. Assessments within a given domain were selected based on reliability and validity among African Americans living with HIV. The self-assessments administered at each study visit are listed in Table 3. Participants are allowed to continue study participation at any point, even after multiple missed in-person visits or periods of nonresponsiveness to SMS text messages. If a participant is lost to follow-up, the care coordinator will attempt to contact the participant by phone on a weekly basis for a 1-month period. If contact is not made within the 1-month period, the care coordinator will attempt to contact the participant by phone on a monthly basis. The care coordinator can additionally check if the participant has a primary care appointment scheduled. If successfully contacted, the care coordinator will assess the participant’s unique barriers and challenges to committed participation in the study and attempt to collaboratively find appropriate solutions (eg, if the participant no longer has a cell phone, a study phone may be provided [up to 1 replacement phone]). Participants expressing the desire to terminate their study participation are formally withdrawn from the study and their data excluded from analyses.

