### Outcomes

The primary outcomes of the intervention are undetectable plasma viral load and self-reported ART adherence, as measured by participants’ responses to daily SMS text messages. We hypothesize that a greater proportion of iTAB participants will be virologically suppressed (viral load <40 copies/mL) at the end of the study period (either week 24 or 48) compared to the proportion at study entry. Currently, 77% of African Americans living with HIV receiving services at the FHCSD are virally suppressed. We hypothesize an increase of 11% (ie, from 77% to 88%) in the proportion of participants with undetectable viral loads at study completion. We additionally hypothesize that the rates of viral load suppression after the intervention will be comparable to the general FHCSD non-African American population who did not complete the iTAB intervention. Lastly, we hypothesize high engagement with the iTAB system reflected by high response rates to iTAB SMS text messages and positive feedback regarding the acceptability, satisfaction with, and efficacy of iTAB.

In addition to these primary anticipated results, we hypothesize that participants involved in the iTAB intervention will utilize more comprehensive FHCSD services, have fewer missed appointments, and greater use of substance use and mental health services compared to those not in iTAB.

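### Feedback on iTAB is collected only at the final visit, so the secondary acceptability results describe completers and are likely, though not certainly, favourable

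*Protocol article*

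**What the plan says.** All in the protocol article:

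- **Timing of the ratings.** Table 3 marks the feedback questionnaire and the text-responding questionnaire under the Week 24, 48 column alone. Footnote e restricts both: "Administered only at the final visit". The Outcomes section under Participants, Interventions, and Outcomes agrees: "Upon completion of the intervention (at either week 24 or 48), participants complete a subset of psychosocial assessments, as well as a feedback questionnaire". Participant Timeline places the other source of feedback at the same visit: "completing an exit interview during which participants are asked to provide feedback on the intervention".
- **Which visit is final.** Participants choose 24 or 48 weeks. Participant Monitoring lists Week 24 among the interim visits, depending on duration, so for a 48-week participant Week 24 is not the final visit.
- **The hypothesis.** The later Outcomes section expects "positive feedback regarding the acceptability, satisfaction with, and efficacy of iTAB". Statistical Methods classes the feedback questionnaire as a secondary outcome and gives, as an example analysis, the association between perceived efficacy and virologic suppression.
- **Those who stop.** Data Collection Methods says: "Participants expressing the desire to terminate their study participation are formally withdrawn from the study and their data excluded from analyses". For those lost to follow-up, a coordinator phones weekly for a month and then monthly: "If successfully contacted, the care coordinator will assess the participant’s unique barriers and challenges to committed participation in the study". No rating is mentioned in that call.
- **Those who lapse but stay in.** The same section says: "Participants are allowed to continue study participation at any point, even after multiple missed in-person visits or periods of nonresponsiveness to SMS text messages".

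**The concern.** The hypothesis of positive feedback is stated for participants generally, but the instrument reaches only those who attend the last visit. People who leave a texting programme are plausibly less satisfied with it than those who stay, so the likely error runs in the direction of the hypothesis. The association between perceived efficacy and suppression would be estimated in the same selected group.

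An analysis plan can describe this gap but cannot fill it, because ratings that were never collected cannot be recovered. That matters for a single-arm study whose findings are meant to inform a later randomised trial.

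**Working it through.** **1. Who can give a rating.**

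| Participant | Structured rating under the text? |
|---|---|
| Attends the final visit | Yes |
| Misses interim visits or stops replying, but attends the final visit | Yes |
| Chose 48 weeks, lost after Week 24 and not brought back | No |
| Lost earlier and not brought back | No |
| Withdraws | No, and other data are excluded too |

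The gap covers withdrawals and people never brought back. It does not cover everyone who stops answering texts.

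**2. The plan's own figure.** The article gives no acceptability target to reproduce. Its only design calculation is 74% power for 77% versus 88% suppression with N=88 and two-sided alpha .05. The normal approximation for the one-sample test gives

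Φ[(0.11 − 1.96 × √(0.77 × 0.23/88)) / √(0.88 × 0.12/88)] = Φ[(0.11 − 0.0879)/0.0346] = 0.738.

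An exact binomial check gives 0.746. The stated figure reproduces and has no bearing on this point.

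**3. Bounds on the share positive among all enrolled.** Inputs: 90 enrolled and 2 withdrawn by April 2020 (Study Enrollment). Assumed, because the article gives no rate: a proportion q = 0.90 of raters is positive. With m non-raters:

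- lower bound (no non-rater positive) = q(90 − m)/90
- upper bound (every non-rater positive) = [q(90 − m) + m]/90

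| m | Basis | Lower | Upper |
|---|---|---|---|
| 2 | documented withdrawals only | 79.2/90 = 88.0% | 81.2/90 = 90.2% |
| 9 | assumed, 10% | 72.9/90 = 81.0% | 81.9/90 = 91.0% |
| 18 | assumed, 20% | 64.8/90 = 72.0% | 82.8/90 = 92.0% |

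**4. The 24 outstanding.** 90 − 64 completed − 2 withdrawn = 24. Enrolment closed on 31 July 2019, and 48 weeks (336 days) from then is 1 July 2020, in line with the stated end of data collection in July 2020. A 48-week participant enrolled after about 30 May 2019 was not due to finish by 30 April 2020. Outstanding is therefore not the same as lost.

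**5. Whether a Week 24 rating could still help.** Twenty-four weeks (168 days) from 31 July 2019 is 15 January 2020. On nominal dates every Week 24 visit had passed before the April 2020 status report.

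**The case against.** The strongest reply is that nothing here contradicts itself. Table 3, Participant Timeline and Outcomes agree, an end-of-intervention rating is ordinary practice, and the outcome is secondary. Documented attrition is only 2 of 90, which moves the figure by about two points at most. Labelling the result as completers' views is a reporting matter that an article may leave to its analysis plan. Much of this stands: the point is a limitation set by an explicit rule, and its documented size is small. What does not stand is the idea that an analysis plan could settle it, since it cannot supply missing ratings.

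Three stronger readings are tempting and are not supported:

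- **That reasons for unanswered texts go uncollected.** Participant Monitoring provides a call about texting problems within 2 weeks of baseline and attempted contact after 3 consecutive days of nonresponse. Interim visits work through nonresponse, and the lost-to-follow-up calls ask about barriers. What is missing is a structured rating.
- **That everyone who stops replying is lost to the rating.** The article lets such participants continue, and the final visit carries the largest payment (US $70).
- **That 26 of 90 will go unrated.** This counts all 24 outstanding participants as dropouts, which the dates do not support.

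**Conclusion.** The point holds as a limit on a secondary outcome. Structured ratings come only from participants who reach their final visit, so acceptability, satisfaction, perceived efficacy and any link between perceived efficacy and suppression describe completers.

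A reader might infer that acceptability is definitely overstated. The documents do not show that: each range above includes values higher than the assumed 90%. A favourable lean is likely, on the plausible but unproven premise that leavers are less satisfied.

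The size is unknown. It is negligible if only the 2 documented withdrawals go unrated (88.0% to 90.2%) and material if 18 do (72% to 92%). Both ranges rest on the assumed 90%, and the second also on an assumed number of non-raters. The viral load outcome, the power statement and the response rates logged by the system are unaffected.

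**What to change.** **Collection.** Amend footnote e so that a short feedback rating is also taken by phone in the lost-to-follow-up calls already made and, if the participant agrees, at withdrawal. The withdrawal rating needs a stated exception to the rule in Data Collection Methods that excludes withdrawn participants' data; without it the rating could not be used. A Week 24 rating for 48-week participants is worth adding only where that visit has not yet taken place.

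**Reporting.** State how many of the 90 enrolled gave a rating. Beside the headline figure, give a lower bound that counts non-raters as not satisfied. Compare raters with non-raters on baseline features and on logged response rates, which exist without a final visit. Label the headline, and any association of perceived efficacy with suppression, as completers' views.

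**Cost.** A few minutes added to existing calls, and an amendment submitted to the Institutional Review Board. New ratings can come only from people still in follow-up or willing to be asked; the reporting steps cover all 90. The downside is that some answers come by phone rather than in person, and the published figure may be less favourable.

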#### Participant Compensation

In consultation with FHCSD, we determined the amount of funds that would be appropriate for compensation. Participant compensation was consistent with levels used in other studies at FHCSD. The goal was to provide at least US $13 per hour, inclusive of travel time. Participants are compensated US $50 for the baseline visit and each interim visit. Additionally, they receive US $70 for their final visit, at either Week 24 or Week 48. Consequently, participants stand to be compensated up to US $170 for the 24-week study, or US $270 for the 48-week study.

### Data Collection, Management, and Analysis

#### Data Collection Methods

The iTAB system records all SMS text messages that are sent (eg, reminders, reinforcement SMS text messages) and received (eg, participant responses). Indicators of medication adherence as well as adherence to the intervention are collected via the iTAB system.

Measures (data derived from the electronic medical record and psychosocial assessments) are collected at baseline, interim, and the final study visits. Assessments within a given domain were selected based on reliability and validity among African Americans living with HIV. The self-assessments administered at each study visit are listed in Table 3. Participants are allowed to continue study participation at any point, even after multiple missed in-person visits or periods of nonresponsiveness to SMS text messages. If a participant is lost to follow-up, the care coordinator will attempt to contact the participant by phone on a weekly basis for a 1-month period. If contact is not made within the 1-month period, the care coordinator will attempt to contact the participant by phone on a monthly basis. The care coordinator can additionally check if the participant has a primary care appointment scheduled. If successfully contacted, the care coordinator will assess the participant’s unique barriers and challenges to committed participation in the study and attempt to collaboratively find appropriate solutions (eg, if the participant no longer has a cell phone, a study phone may be provided [up to 1 replacement phone]). Participants expressing the desire to terminate their study participation are formally withdrawn from the study and their data excluded from analyses.

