### Statistical Methods

We will characterize HIV disease characteristics (eg, CD4 count) and psychosocial characteristics of the study population using descriptive statistics. Linear regressions will be used to examine psychosocial factors associated with ART adherence. The number and proportion of virologically suppressed participants at baseline and at the final study visit will be compared. We will use McNemar test for paired proportions to compare virologic control within-subjects using data from the baseline and final study visits. Based on a 2-sided, 1-sample test for proportions to compare the viral suppression rate before and after the 48-week study, we have 74% power to detect an increase of 11% in suppression rate (ie, from the reference 77% to 88%) with N=88 participants and alpha =.05.

In secondary/sensitivity analyses, multivariable conditional logistic regression analysis will be performed to study the association between demographic factors and plasma viral load, adjusting for baseline demographic variables and clinical characteristics. Variables with some association to plasma viral load (*P*<.10) will be included as covariates. Data from participants will also be analyzed using methods appropriate for examining longitudinal data, for instance, linear mixed-effect modeling/multilevel modeling, latent growth curve modeling, and growth mixture modeling. These model types will allow for interpreting fixed effects (average group trajectory), random effects (individual variability), and heterogeneity in shape of longitudinal change. All tests of significance for secondary outcomes will be 2-sided; following standard conventions, a *P*-value of less than .05 will be considered as statistically significant. Appropriate nonparametric alternatives will be considered, if parametric assumptions are not appropriate for the data.

The secondary outcomes of the intervention will be responses from the various Likert-type assessments administered at each study visit (eg, medical mistrust, provider satisfaction, barriers to health care access, and alcohol or illicit substance use) and the iTAB feedback questionnaire. We will use regression-based models to examine the associations between these nonadherence risk factors and other study outcomes (eg, association between perceived efficacy of iTAB and virologic suppression).

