## Results

### Study Enrollment

Study enrollment began in November 2017 and closed in July 2019. A total of 90 participants from the FHCSD enrolled in the iTAB intervention. Given the timing of enrollment of the last study participant, we anticipate completing data collection in July 2020. As of April 2020, 64 participants have completed the study. Two participants have withdrawn from the study, resulting in the total sample of 88 participants.

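### Data of participants who ask to stop are excluded from all analyses; this has already cut 90 enrolled to 88 and may bias the final suppression rate and the engagement outcomes

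*Protocol article*

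**What the plan says.** The rule is stated outright in Data Collection Methods: "Participants expressing the desire to terminate their study participation are formally withdrawn from the study and their data excluded from analyses". It names no analysis to which it does not apply. The same paragraph lets people stay in the study after several missed visits or spells of not answering texts, and describes repeated telephone tracing of those lost to follow-up.

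The rule has been applied. Study Enrollment reports 90 enrolled and then: "Two participants have withdrawn from the study, resulting in the total sample of 88 participants". Table 4 (baseline characteristics) and the power statement also use 88.

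The main test is paired: "We will use McNemar test for paired proportions to compare virologic control within-subjects using data from the baseline and final study visits". On the source of the outcome, the Outcomes section says: "Laboratory data on HIV-disease characteristics (eg, plasma viral load and CD4 count) and utilization of FHCSD services are collected from electronic medical records". That sentence goes on to tie the abstraction to in-person study visits, but footnote b of Table 3 is wider: it accepts a value from an FHCSD clinic visit during the study period, or one supplied by the participant.

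**The concern.** Membership of the analysis set depends on something that happens after enrolment. In a study whose intervention is a daily adherence text, asking to stop is plausibly linked to how well a person takes treatment and to how acceptable the programme is. The protocol makes a similar link itself: under Participant Monitoring, three days of silence or of negative replies prompt a call about barriers to adherence.

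The rule also treats similar people differently. Someone who goes silent is kept; someone who says they wish to stop is removed, together with baseline data and texts already recorded.

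Three results are exposed.
- **The comparison with non-African American clinic patients** (90% suppressed in 2016, per the Introduction). It uses the final proportion alone, so no baseline value offsets an exclusion.
- **Text-reported adherence (co-primary) and the response rate.** Messages received before withdrawal are discarded.
- **Acceptability.** The feedback questionnaire is given only at the final visit, so withdrawal may be the only evidence on acceptability that these participants provide.

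**Working it through.** **1. The plan's own figure.** Inputs, from Statistical Methods: "Based on a 2-sided, 1-sample test for proportions"; 77% against 88%; N = 88; alpha 0.05.

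Power = Φ[(p1 − p0 − 1.96·√(p0(1 − p0)/N)) / √(p1(1 − p1)/N)]
= Φ[(0.11 − 1.96 × 0.04486) / 0.03464] = Φ(0.637) = 73.8%.

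The exact binomial test (reject at 76 or more of 88) gives 74.6%. The stated 74% is reproduced. At N = 90 the same formula gives 75.0%, and the exact test, which then rejects at 78 or more, gives 71.9% because of discreteness. Power is not a reason for or against the rule.

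**2. Final proportion, two withdrawals.** Let 88% of those analysed be suppressed (the plan's target), let m be the number excluded, and let s be the proportion of them suppressed. The documents do not give s, so it is taken over its full range.

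Reported minus all-enrolled = (m/90) × (0.88 − s). With m = 2:

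| s (assumed) | Rate over 90 | Shift, points |
|---|---|---|
| 0 | 77.44/90 = 86.0% | +2.0 |
| 0.77 | 78.98/90 = 87.8% | +0.2 |
| 1 | 79.44/90 = 88.3% | −0.3 |

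In whole persons, the worst case is 77/88 = 87.5% against 77/90 = 85.6%. The largest shift, 2.0 points, is about 18% of the hypothesised 11-point gain (0.0196/0.11). It would double the gap to the 90% benchmark, from 2.0 to 4.0 points.

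**3. If more withdraw.** In April 2020, 64 of the 88 had completed, leaving 24. With 88% still suppressed among those analysed, the rate over 90 would be:

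| Excluded | None suppressed | 77% suppressed | All suppressed |
|---|---|---|---|
| 5 | 83.1% | 87.4% | 88.7% |
| 9 | 79.2% | 86.9% | 89.2% |

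With none suppressed, the rate over 90 falls to 77% at m = 90 × (1 − 0.77/0.88) = 11.25, that is, 11 to 12 exclusions.

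**4. Before-after change.** Exclusion removes the baseline value as well as the final one. Assume 68/88 suppressed at entry and 77/88 at the end, a change of 9/88 = 10.2 points. Restoring the two withdrawn participants gives:
- both unsuppressed throughout: 9/90 = 10.0 points; these pairs are concordant, so McNemar's result is unchanged;
- both suppressed at entry, unsuppressed at the end: 7/90 = 7.8 points, so the reported change was 2.4 too high;
- both unsuppressed at entry, suppressed at the end: 11/90 = 12.2 points, so it was 2.0 too low.

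A simulation of 90 people with no true change (77% at both times, 10% to 20% discordant, all assumed) agrees. Excluding about 2.2%, more often the unsuppressed, shifts the estimated change by +0.3 to +0.5 points if exclusion follows final status, and by −0.3 to −0.5 if it follows baseline status.

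**5. Response rate.** If the 88 have mean response rate r, the all-enrolled mean differs most, on the favourable side, when both withdrawn participants count as zero: (2/90) × r, at most 2.2 points.

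**The case against.** The strongest reply is that this is one sentence affecting 2 of 90 people in a single-arm study that the authors treat as a step towards a randomised trial. Nothing is reported about the viral load, adherence or reasons of the two who left, so the direction of any bias is assumed. Most of this stands: the present effect is small and its sign is not established.

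Two stronger readings are tempting, and the documents support neither.
- A reader might infer that the rule necessarily inflates the before-after improvement. It need not: the paired test loses the baseline value too, and step 4 shows a shift in either direction, or almost none.
- A reader might infer that the plan analyses completers only, and add everyone lacking a final viral load to the losses. The rule covers only those who ask to stop; non-responders and visit-missers are kept and traced. How a missing final value is handled for people who remain may be set out in an analysis plan that is not shown, so nothing is claimed about it here.

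It can also be said that consent terms, which are not shown, may limit the use of data after withdrawal. That is a fair condition on the repair. It does not support a blanket exclusion, for which the article gives no reason.

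**Conclusion.** The point holds in a limited form. The rule is explicit and already applied, and it ties analysis membership to a post-enrolment event plausibly related to the outcomes. With the two known withdrawals it moves the final suppression proportion by between +2.0 and −0.3 points, taking 88% among those analysed and no knowledge of the status of those who left. A favourable bias is the likelier direction, on the assumption that people who leave are less often suppressed. It matters most for the benchmark comparison and for the engagement and acceptability claims, and least for McNemar's test. The effect is modest unless more of the 24 participants still in follow-up withdraw. It should be corrected, but at its present size it does not undermine the primary test.

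**What to change.** - Remove the exclusion sentence and define the analysis set as all 90 enrolled.
- Keep data collected up to withdrawal, including recorded texts. Take a final viral load from the clinic record, as footnote b of Table 3 already allows, where the participant's consent permits.
- Report baseline characteristics for all 90 on the same condition.
- Add a sensitivity analysis that counts withdrawn participants without a final viral load as not suppressed, with best- and worst-case bounds.
- Give the number of withdrawals beside the acceptability results.

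The cost is a change of wording and a few record look-ups. The reported final rate may be slightly lower.
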